## Introduction

### Out-of-Hospital Cardiac Arrest

Out-of-hospital cardiac arrest (OHCA) describes the sudden loss of mechanical function of the heart and the absence of blood flow around the body, occurring outside of a hospital setting
^
1,
2
^. OHCA is the most time-critical medical emergency, with survival depending on the prompt actions of the community where OHCA occurs, emergency medical services (EMS) and in turn, appropriate follow-on hospital care
^
3
^. Internationally, the annual incidence of OHCA treated by emergency medical services (EMS) is estimated to be 30 – 97 individuals per 100,000 population, median age ranges from 64 to 79 years and more than half of victims are male
^
4
^. OHCA with attempted resuscitation has an incidence of 56 per 100,000 population per year in Europe and is considered the third leading cause of death
^
5
^. Survival to/ immediately after hospital discharge ranges from three to twenty percent internationally and is eight percent in Europe
^
6
^. Of those that do survive to discharge in Europe and North America, approximately seventy percent are still alive at three years
^
7
^. In Ireland there are now almost 3,000 OHCAs with attempted resuscitation each year of which six to seven percent involve survival to hospital discharge
^
8
^.

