### Out of Hospital Cardiac Arrest & Quality Improvement Registries

The science underpinning the ‘chain of survival’ is unquestionably of critical importance in OHCA care. However, scientific research alone will not be sufficient to improve OHCA outcomes and must be accompanied by a focus on real world implementation and quality improvement
^
24
^. To this end the European Resuscitation Council recommend that ‘health systems should have population-based registries which monitor the incidence, case-mix, treatment and outcomes for cardiac arrest’ and that these data ‘should inform health system planning and responses to cardiac arrest’
^
25
^.

An internationally agreed ‘Utstein’ registry dataset has been devised which facilitates national and international comparison of OHCA
^
26
^. A recent pan European survey reported that six countries (including Ireland) had an OHCA registry with full population coverage, fourteen had partial population coverage and seven countries reported not having an OHCA registry
^
27
^. Comprehensive data on the Irish experience of OHCA is provided by the Irish Out-of-Hospital Cardiac Arrest Registry (OHCAR). OHCAR achieved national coverage using the Utstein dataset in 2012, and by 2020 this contains over 20,000 cases. In terms of the period considered in this study OHCAR does not include OHCA with EMS response but without attempted resuscitation. We anticipate that approximately fifty percent of cases recorded in OHCAR are witnessed (European average 66%), and twenty percent have an initial ‘shockable rhythm’ (European average 20%)
^
6
^. The primary sources of OHCAR data are patient care records and dispatch data from Ireland’s statutory ambulance services. OHCAR has provided invaluable continuous quality improvement data on an annual basis to ambulance services. To date however, no temporal analyses have been conducted to assess the impact of national interventions on survival in Ireland. Nor has the database been interrogated to determine whether international trends in OHCA (including increased bystander CPR and associated survival improvements
^
28–
30
^) are mirrored in the Irish data.

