**Figure 1. f1:**
[figure not shown]
OHCA Health System Developments in Ireland 2012–2020. NAS: National Ambulance Service, QI: Quality Improvement, PAD: Public Access Defibrillation, CPR: Cardiopulmonary Resuscitation, CFR: Community First Responder, GP: General Practitioner, OHCA: Out-of-Hospital Cardiac Arrest.

 In 2015 and 2016 the National Ambulance Service transitioned from a system of multiple regional independent control centres to a single national control centre (NEOC). This significant change allowed an enhanced level of resource co-ordination and further allowed dispatch assisted CPR to be fully embedded as a standard of care at national level. Between 2016 and 2020 the Irish Heart Foundation ‘CPR 4 schools’ programme trained 1,827 teachers in 531 schools to perform CPR training for a potential 288,197 students. Between 2016 and 2020 lay community first responder groups increased from 100 to 175 nationally. In 2017 the NAS created four new Community Engagement Officer posts to support CFR activities and expansion. Also between 2016 and 2020 GP (general practitioner) first responder numbers doubled to almost 200 individuals
^
40
^. The final year of this study period 2020 is exceptional in that it represented the first year of the Covid-19 pandemic, the first wave of which occurred between February and July 2020
^
41
^. The Irish health service responded by introducing a range of public health measures including travel restrictions, schools and business closure, cessation of large indoor gatherings, and other social distancing measures
^
42
^. In terms of OHCA, internationally Covid-19 is known to have detrimentally affected systems of care and was associated with prolonged EMS response and worse short-term outcomes including survival compared to pre-pandemic periods
^
43
^. The effects of COVID-19 on OHCA in Ireland have not yet been systematically evaluated; however similar trends are probably likely. Thus, it is necessary to consider this as a significant OHCA development in the 2020 period.

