### Focus of this study

This study will examine data from the Irish Out-of-Hospital Cardiac Arrest Registry (OHCAR) to describe OHCA incidence and its care processes in Ireland over the period 2012 to 2020. We will further interrogate this data to identify key OHCAR variables that predict key outcomes. We anticipate approximately 18,000 relevant observations will be available for analysis. We will consider survival to hospital discharge, bystander CPR, and bystander defibrillation to be key outcomes of interest over the study period. We hypothesise that of the timeline of OHCA developments described above, two key developments are likely to be associated with a significant change in outcomes. Given the scale of reorganisation and centralisation of EMS control in 2015 and 2016 on the backdrop of the ongoing NAS ‘one life’ project we hypothesise that the NAS transition from a system of multiple regional independent control centres to the single national control centre (NEOC) would be associated with improvements in bystander CPR and survival to hospital discharge. In turn, given Covid-19’s detrimental effect on OHCA internationally we hypothesise that COVID-19 would be associated with significant reductions in bystander CPR, bystander defibrillation and survival to hospital discharge in Ireland.

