### Variables and categories of concern

All analysis will be based on the variables shown in
Table 1. Variables 1–19 will be obtained from the OHCAR. Variables 20, 21 and 22 represent component time periods that are a priori considered to be potentially significant in the context of either system level developments or key population health challenges (Covid-19) during the study time period. Variables 20,21 and 22 will be dummy variables created using the ‘Year’ variable. Variables 20 and 21 will be linked dummy variables derived from the same 3-level categorical indicator of period and will be simultaneously included in regression models. We do not expect collinearity of these predictors, as transition and post-transition period correspond to years 2015 and 2016, and 2017 through 2020, respectively. The Covid period dummy variable (variable 22) will be an indicator of 2020 only, and thus should allow us to estimate any shift in survival in the final year of the study data.
Table 1 highlights the independent variables that will be explored for each outcome of interest. Where an original OHCAR variable has multiple potential associated categories, we will collapse these categories to avoid decreased statistical power from analysis of an excessive number of potentially sparse categories. Original and collapsed categories are shown in
Table 1. Season will represent the ‘winter’ healthcare period (October to March) as compared to other as ‘winter’ is a period of increased demand for the Irish healthcare service. The three time categories chosen are adopted based on previous OHCA research
^
44
^. Home (versus other) location was chosen as home represents the most common location for OHCA in Ireland. ‘Year’ (variable 9) will be treated as a continuous variable to conserve degrees of freedom and statistical power.

**Table 1. T1:** Variables for analysis.

Variable Number	Variable	Categories	Collapsed Categories	Outcome of Interest		
				Bystander CPR	Bystander Defibrillation	Survival to Hospital Discharge
**1**	**Airway** ** Management**	**Basic ** **Management**	**None of the listed devices ** **used, OPA/NPA, No advanced** ** airway**			*****

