		**Not Covid Period**				

### Statistical model building and interpretation procedures

For each outcome we will build a logistic model: initially a full model with all relevant predictors will be fitted. A refined model will then be built using a stepwise model selection procedure (STEPAIC function in R). This procedure builds several models from all possible combinations of the predictors by sequentially adding and dropping predictors and finally selects the model with the lowest AIC. The stepwise model will then be further improved by examining addition of pairwise interaction variables and retaining any interactions which improve fit. We will evaluate each model (full, stepwise and with interactions) based on AIC. In addition, the model deviance and a Hosmer-Lemeshow Goodness of Fit (GOF) test will be inspected for each model. To assess linearity between continuous predictors and the log odds of the outcome we will rely on good model fit as indicated by the Hosmer-Lemeshow goodness of fit test. We will also use logistic regression with higher order terms (polynomial terms) to explore if the relationship between the outcome and the continuous predictors is indeed non-linear. If higher-order terms are significant, these will be retained in the model, otherwise they will be dropped from the model. We will also attempt to ameliorate fit by including pair-wise interaction terms between predictors. We will summarise the effect of each individual variable in the final model using odds ratios and 95% confidence intervals. The effect of any significant interactions in the final model will be explored graphically. After selecting the final model from the three models, we will evaluate the predictive ability of the final best fitting model using 10-fold cross-validation and evaluate the prediction accuracy for the model.

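### The survival model's period and Covid odds ratios leave out whatever acts through bystander CPR, first shock and response interval, so they do not estimate the overall change in survival that aims 3 and 4 ask about

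*Protocol article*

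**What the plan says.** Under Study aims, aim 3 asks whether the 2015–2016 move to a single control centre was associated with better bystander CPR, bystander defibrillation and survival. Aim 4 asks about the effect of Covid on the same three outcomes. The text introducing Table 1 adds that the 2020 indicator should show whether survival shifted in the final year.

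Table 1 "highlights the independent variables that will be explored for each outcome of interest". Its survival column contains:

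- variables 20–22: transition, post-transition and Covid dummies, plus Year (variable 9);
- variables 12, 10 and 5: who started compressions, first shock, call response interval;
- variables 1, 7, 11, 14, 18 and 19: airway, mechanical CPR, initial rhythm, number of shocks, adrenaline, amiodarone.

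Of the last two groups, only call response interval also appears in the two bystander columns.

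On mechanism, the section on health system developments says that the control-centre change improved co-ordination of resources and "further allowed dispatch assisted CPR to be fully embedded as a standard of care at national level". It also cites international evidence that Covid lengthened EMS response. Focus of this study hypothesises that the control-centre change "would be associated with improvements in bystander CPR and survival to hospital discharge", and that Covid lowered bystander CPR, bystander defibrillation and survival.

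On modelling, "initially a full model with all relevant predictors will be fitted", followed by stepwise AIC selection and interactions. Odds ratios are then reported from the one final model for each outcome. No survival model without the care variables is described.

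**The concern.** For survival, the protocol names bystander CPR (both exposures), bystander defibrillation (Covid) and response time (Covid explicitly, the control-centre change through resource co-ordination) as things the exposures change. It then holds these constant when it estimates the exposures' association with survival. A period odds ratio from that model compares patients in different periods who had the same bystander CPR, first-shock and response-interval values. That is a legitimate quantity, but it is not the overall change in survival.

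A gain delivered through more bystander CPR, or a Covid loss delivered through slower response, would be credited to those variables and not to the period. A period odds ratio near 1 could then be produced by the adjustment. The Discussion intends the results to inform the design of community emergency care, so the distinction matters to readers.

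**Working it through.** The documents give no effect size, power or bystander CPR rate, so there is no stated figure to reproduce. Everything below that is not marked as theirs is an assumption.

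**Inputs from the protocol article**

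- "We anticipate approximately 18,000 relevant observations will be available for analysis" (Focus of this study).
- Of attempted resuscitations, "six to seven percent involve survival to hospital discharge" (Introduction). Applying this to the study cohort is an assumption: 18,000 × 0.06 = 1,080 and 18,000 × 0.07 = 1,260 survivors.
- "approximately fifty percent of cases recorded in OHCAR are witnessed" and "twenty percent have an initial ‘shockable rhythm" (registry section). These informed the simulation in step 3.

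**Step 1. CPR as the only route**

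Survival in a period = (1 − a)·s0 + a·s1, where a is the bystander CPR rate, s0 and s1 are survival without and with it, and odds(s1) = OR × odds(s0).

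Assume s0 = 3% and OR = 2.5. Then s1 = 7.18%.

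- a from 65% to 80%: survival goes from 5.72% to 6.34%, total period OR 1.12.
- a from 60% to 85%: survival goes from 5.51% to 6.55%, total period OR 1.20.

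With CPR in the model the period OR is 1.00 in both cases. That follows from assuming no other route.

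**Step 2. Adding a direct effect**

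Overall survival is set to 6.5%. The CPR rate rises 60→70%, 60→80% or 50→80%, and the CPR–survival OR is 1.5, 2 or 3. Share removed = 1 − log(adjusted OR)/log(total OR).

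| Direct OR | Total OR | CPR-adjusted OR | Share of log OR removed |
|---|---|---|---|
| 1.0 | 1.04 to 1.31 | 1.00 | 100% |
| 1.2 | 1.25 to 1.57 | 1.20 | 17% to 59% |

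The ends of the second row are 1 − 0.1823/0.2199 = 0.17 and 1 − 0.1823/0.4498 = 0.59.

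**Step 3. Several mediators together**

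This used 200 simulated registries of 18,000 records over nine years, with assumed effects through CPR, rhythm, bystander first shock and response interval. Year was left out to isolate the adjustment.

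| Scenario | Term | Without care variables: OR (rejected) | With care variables: OR (rejected) |
|---|---|---|---|
| No direct effect | Post-transition | 1.13 (41%) | 1.00 (6%) |
| No direct effect | Covid | 0.86 (28%) | 1.00 (6%) |
| Direct post-transition OR 1.16 | Post-transition | 1.30 (95%) | 1.16 (48%) |

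**Step 4. What a case-mix model can show once Year is kept**

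Assume 2,000 cases a year, 6.5% survival and no other covariates. Information per year = 2,000 × 0.065 × 0.935 = 121.55.

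- Without Year, the post-transition term contrasts 2017–2019 with 2012–2014, because 2020 has its own term. SE(log OR) = √(2/(3 × 121.55)) = 0.074.
- With Year added linearly, inverting the information matrix gives SE = 0.226.
- Two-sided 5% power with Year, from z = log(OR)/0.226: 8% for OR 1.12, 13% for OR 1.20, 21% for OR 1.30.
- For Covid with Year, SE = 0.135. Power for OR 0.86 is 20%.

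**The case against.** Several points on the other side stand.

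- **Scope.** A reader might infer that aims 3 and 4 fail for all three outcomes. They do not. The bystander CPR and bystander defibrillation models contain none of variables 1, 7, 10–12, 14, 18 and 19, so the dispatch-assisted CPR route is tested directly in the bystander CPR model. Only call response interval is in question there. The protocol does not say that EMS response time changes whether a bystander acts, so the case for dropping it is thin.
- **Pathways.** A reader might infer that every care variable in the survival model is a proven mediator. The documents name no route from either exposure to rhythm, airway, mechanical CPR, number of shocks or drugs. If wider use of mechanical CPR was a separate concurrent change, adjusting for it is defensible, and leaving it out could credit it to the transition.
- **Size.** A reader might infer that the whole effect is removed. That holds only if no unadjusted route exists.
- **Detection.** With Year retained, power of 8–21% means the case-mix model would often be non-significant too.
- **Mitigation.** Descriptive summaries and graphs would show a crude change in survival, and the aims are worded as exploratory.

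The rest of the defence is weaker. Modelling predictors is a proper aim (aim 2), but the article describes no separate model for aims 3 and 4. Stepwise AIC might drop some mediators, but strong predictors of survival will probably stay. If they do not, the meaning of the period odds ratio depends on the selection. Crude graphs give no case-mix-adjusted estimate. The limitations in the Discussion mention confounding and unexplained variation, not adjustment for consequences of the exposure.

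**Conclusion.** The point holds for survival to hospital discharge. The planned period and Covid odds ratios exclude whatever acts through the adjusted variables, so they do not estimate the overall change in survival that aims 3 and 4 ask about. The support is strongest for bystander CPR, first shock and response interval, which the protocol links to one or both exposures. For the remaining care variables it is an inference.

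The size cannot be fixed from the documents. Under the assumed CPR rates and CPR–survival odds ratios, the loss runs from about 17–59% of the log odds ratio with a direct odds ratio of 1.2, up to all of it if every route is adjusted for. Complete loss is the extreme case and not the expected one.

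The documents do not support extending this to the two bystander outcomes, beyond a possible role for response interval. Nor do they support expecting that the corrected model would usually turn a null result into a detection. It corrects what is estimated and adds little certainty.

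**What to change.** Prespecify a separate survival model for aims 3 and 4 containing:

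- Year, the three-level period and Covid, with the period and Covid terms forced in and not open to stepwise removal;
- case-mix fixed before the response only: age, sex, aetiology, location, witnessed status, urban/rural, season, time of day, weekday/weekend.

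Read the period and Covid odds ratios for survival from this model, with their confidence intervals. Keep the wider model for aim 2, and label its period and Covid coefficients as conditional (direct) associations. In the two bystander models, rerun without call response interval as a sensitivity analysis.

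The cost is a few lines of methods text, one extra survival model and the bystander sensitivity runs, with no new data. The downsides should be stated with the results: the case-mix model does not separate concurrent changes in care from the transition, and with Year retained its period estimate stays imprecise, so a non-significant result must not be reported as no effect.

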		**Supraglottic** ** airway device**				
		**Intubation**				
**2**	**Aetiology**	**Presumed Other**	**Trauma, Respiratory, ** **Submersion, Non-cardiac, ** **Other**	*****	*****	*****
		**Presumed Cardiac**				
**3**	**Age**	**Age (years)**		*****	*****	*****
**4**	**Sex**	**Female**		*****	*****	*****
		**Male**				
**5**	**Call Response** ** Interval**	**Call Response** ** Interval (minutes)**		*****	*****	*****
**6**	**Incident location**	**Other Location**	**Industrial, Public building, GP** ** Surgery, Farm, Sport place,** ** Residential institution, Street,** ** Ambulance, Other**	*****	*****	*****
		**Home Location**				
**7**	**Mechanical CPR**	**No Mechanical ** **CPR Provided**				*****
		**Mechanical CPR** ** Provided**				
**8**	**Season**	**Winter**	**October–March**	*****	*****	*****
		**Other**	**April–September**			
**9**	**Year**	**Year (continuous** ** variable** ** 2012–2020)**		*****	*****	*****
**10**	**First Shock ** **Delivered By**	**Not Applicable**				*****
		**Bystander** ** Defibrillation**				
		**EMS Defibrillation**				
**11**	**Shockable Initial** ** Rhythm**	**Non-Shockable** ** Initial Rhythm**				*****
		**Shockable Initial ** **Rhythm**				
**12**	**Chest ** **Compressions ** **Started By**	**EMS initiated CPR**				*****
		**Bystander CPR**				
**13**	**Time of Day**	**Night**		*****	*****	*****
		**Evening**				
		**Morning**				
**14**	**Total No of Shocks** ** Delivered**	**Total No of Shocks ** **Delivered**				*****
**15**	**Who Witnessed** ** Collapse**	**Not Witnessed**		*****	*****	*****

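### In the survival model the shock count sits beside a first-shock variable with a no-shock level, so odds ratios against Not Applicable are extrapolated to zero shocks

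*Protocol article*

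**What the plan says.** Table 1 (under Variables and categories of concern) marks the candidate predictors for each outcome. Two shock variables are marked for survival to hospital discharge, and for that outcome only:

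- Variable 10, "First Shock Delivered By", with three levels: "Not Applicable", "Bystander Defibrillation" and "EMS Defibrillation".
- Variable 14, "Total No of Shocks Delivered", with no categories, so apparently a numeric count.

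Under Statistical model building and interpretation procedures, "initially a full model with all relevant predictors will be fitted". Then "A refined model will then be built using a stepwise model selection procedure (STEPAIC function in R"), after which pairwise interactions and polynomial terms for continuous predictors are explored. On reporting: "We will summarise the effect of each individual variable in the final model using odds ratios and 95% confidence intervals".

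The article does not define Not Applicable, does not say whether the total includes shocks given by bystanders, and does not name a reference level. It does not tie the count to shocked patients, and it does not bar the two variables from standing together.

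**The concern.** An odds ratio from a model that holds both variables is read at a fixed value of the other. For variable 10 this means comparing a patient defibrillated by a bystander or by EMS with an unshocked patient who has the same number of shocks. On the natural reading of the levels, no such pair exists. The coefficient can still be estimated, because the count varies among shocked patients, but it describes a defibrillated patient with zero shocks.

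A reader of the results table would probably take the bystander-defibrillation odds ratio as the gain from a bystander shock over no shock. Its value would in fact move with the per-shock slope. The planned checks (AIC, deviance, Hosmer-Lemeshow, 10-fold cross-validation) would not reveal this, because they look at fitted values and not at what a coefficient means.

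**Working it through.** The plan gives no figure on this point, so there is none to reproduce. The check has three steps.

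**1. Values that each group can take.** Not Applicable: count = 0. Bystander or EMS defibrillation: count = 1, 2, 3, ... The two sets share no value. This assumes that Not Applicable means no shock and that the total counts all shocks.

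**2. Algebra.** Let b10 be the coefficient of a shocked level against Not Applicable, b14 the coefficient per shock, and t the total. For a shocked patient:

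b10 + b14·t = (b10 + b14) + b14·(t − 1)

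The log odds ratio for exactly one shock versus none is b10 + b14, but the planned table shows b10. Hence

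reported OR = exp(b10) = (one-shock-versus-none OR) × 1/(OR per shock).

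For a shocked patient the recoded count u = t − 1 gives the same linear predictor, and unshocked patients have 0 under both codings. Fitted values, AIC and all other coefficients are therefore identical. The bystander-versus-EMS log odds ratio is a difference of two b10 terms, so b14 cancels. With a squared term (coefficient c14), the one-shock contrast is b10 + b14 + c14, and the two codings are again equivalent.

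This equivalence is for main effects and polynomials. If the count is given an interaction with a third variable, the codings agree only if variable 10 also interacts with that variable. If variables 10 and 14 interact with each other, the bystander-versus-EMS odds ratio also depends on the count at which it is read.

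**3. Illustration.** From the document: about 18,000 observations (Focus of this study), survival of 6–7% and about 20% with a shockable first rhythm (Introduction). Assumed, not in the document: 75% unshocked, 7% first shocked by a bystander, 18% by EMS; shocks = 1 + Poisson(2) if shocked; survival of 2% unshocked, and 27% (bystander) and 20% (EMS) at one shock. The simulated one-shock bystander OR is (0.27/0.73)/(0.02/0.98) = 18.1; the EMS one is (0.20/0.80)/(0.02/0.98) = 12.25. Estimates come from 20 × 18,000 simulated records.

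| Log-odds slope per extra shock | 1/(OR per shock) | Bystander OR, total count | Bystander OR, shocks after first | Ratio | Bystander vs EMS, both codings |
|---|---|---|---|---|---|
| −0.30 | 1.35 | 24.21 | 17.93 | 1.35 | 1.47 |
| −0.15 | 1.16 | 20.98 | 18.10 | 1.16 | 1.47 |
| 0 | 1.00 | 18.20 | 18.10 | 1.01 | 1.47 |
| +0.15 | 0.86 | 15.35 | 17.88 | 0.86 | 1.48 |

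The EMS odds ratio behaves alike: 16.46, 14.31, 12.34 and 10.36 with the total count, against 12.19, 12.35, 12.27 and 12.08 with the recoded one. A squared term in the total count does not cure it (bystander OR 24.41, 21.42, 18.08, 15.82).

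A second simulation of 18,000 records (assumed: 28% shocked, 22% of those first by a bystander, 1 + Poisson(2.2) shocks) agrees. At a fitted OR per shock of 0.825 the bystander OR was 7.32 against 6.04 (ratio 1.21 = 1/0.825), with AIC 6275.6 under both codings. At 0.729 it was 10.11 against 7.37 (ratio 1.37 = 1/0.729), with AIC 5695.5 under both.

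**The case against.** **Reference level.** It is not stated, and the order of levels in Table 1 does not settle it: variables 20 to 22 list the exposed period first. The alphabetical default in R would make bystander defibrillation the reference and print EMS versus bystander directly, which is sound. This stands, but it only moves the problem: the Not Applicable coefficient would then be the affected one.

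**Definitions.** The registry draws mainly on ambulance and dispatch records (Introduction). If bystander shocks are missing from the total, a bystander-first patient could have a recorded count of 0, and the separation would weaken for that level. The word total speaks against this, and the EMS level would still be affected.

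**Not a model fault.** Recoding leaves predictions, cross-validation and the transition and COVID-19 terms unchanged. This is right for models without interactions involving the count; the fault lies in how one set of odds ratios is read.

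**Selection.** Stepwise AIC may drop one of the two variables. True, but the full model holds both and nothing prevents both being kept. The objection does limit the remedy: in a candidate without variable 10, the recoded count would treat zero shocks and one shock as the same.

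**Left to an analysis plan.** Reference levels and derived coding often are. But this article fixes the predictors, the levels of variable 10 and the form of reporting, and following them as written gives the misleading number.

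**Stronger readings to avoid.** A reader might infer that the bystander benefit will be inflated. The document does not support that, because the direction depends on the sign of the per-shock slope, which it does not give. A reader might also take this as a main result. Study aims speaks of exploring predictors of three outcomes, and the stated hypotheses concern the control-centre transition and COVID-19; no defibrillation contrast is singled out.

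**Conclusion.** The point holds as one of interpretation. As planned, any odds ratio contrasting bystander or EMS defibrillation with Not Applicable in a survival model that also holds the shock count is an extrapolation to zero shocks. With a linear count it differs from the one-shock-versus-none odds ratio by exactly the factor 1/(OR per shock).

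This rests on three readings that the article suggests but does not state: Not Applicable means no shock, the total counts all shocks, and the count enters as a number. The factor is algebra; the absolute odds ratios in the illustration are not a forecast. They rest on assumed inputs and omit other planned predictors such as initial rhythm, adrenaline and amiodarone.

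The change is worth making because it costs almost nothing and the planned fit checks cannot show the need for it.

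**What to change.** 1. State that Not Applicable means no shock and that the total includes bystander shocks. Before recoding, check that no patient at the bystander or EMS level has a count of 0, since the recode would give −1.
2. In the full model, and in any selected model that keeps both variables, report variable 14 as shocks after the first: 0 if Not Applicable, total minus 1 otherwise. Build any polynomial on this recoded count. The variable 10 odds ratios then compare exactly one shock with none.
3. State the reference level, and report bystander versus EMS beside the contrasts with no shock, since those two groups do overlap on shock count.
4. Keep the total count in stepwise candidates that omit variable 10. A simple route is to run the selection on the total count and refit with the recoded count if both variables survive.
5. If an interaction involving the count is retained, state the count at which the variable 10 odds ratios are read.

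Cost: one derived variable and one more reported contrast, with no new data. The odds ratios versus no shock may become less favourable.
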